# **List of Abbreviations**

**AIDS** Acquired Immune Deficiency Syndrome

**ADLHIV** Adolescents living with HIV

**ANOVA** Analysis of Variance

**ART** Antiretroviral Therapy

**BP** Blood Pressure

**CAVI** Cardio-Ankle Vascular Index

**CPD** Continuous Professional Development

**CPG** Clinical Practice Guidelines

**CVD** Cardiovascular Disease

**DBP** Diastolic Blood Pressure

**GHS** Ghana Health Service

**HCW** Healthcare worker

**HIV** Human Immunodeficiency Virus

**NHBPEP** National High Blood Pressure Education Program

**PLHIV** Persons living with HIV

**SBP** Systolic Blood pressure

**STG** Standard Treatment Guidelines

**TPB** Theory of Planned Behavior

**TRA** Theory of Reasoned Action

**WHO** World Health Organization

# **Study Summary**

**Background:** Recent studies have shown a relatively higher incidence of cardiovascular diseases and related deaths among persons living with HIV than uninfected persons. The adverse effects of some antiretroviral medication, chronic vascular inflammation, and immune activation from persistent HIV replication leading to arterial stiffness contribute to this. The duration of exposure to the virus plays a vital role in the pathogenesis, putting perinatally infected children and adolescents at higher risk than behaviorally-infected individuals. This, therefore, supports the calls for increased surveillance of NCDs, especially hypertension among them.

**Aim and objectives:** The overall aim of the study is to improve the adherence of healthcare workers to the guidelines for screening and management of hypertension among adolescents living with HIV(ADLHIV) at selected ART sites in the Greater Accra Region. The objectives are to

1. Determine the factors influencing health care workers' adherence to the guidelines for screening and management of hypertension among ADLHIV.
2. Assess the effect of a Theory of Planned Behavior-based intervention on healthcare workers' adherence to guidelines for screening & management of hypertension among ADLHIV.
3. Assess the effect of a Theory of Planned Behavior-based intervention on the arterial stiffness and blood pressure of ADLHIV.

**Methodology:** The study will be conducted among 24 antiretroviral therapy sites in the Greater Accra Region. An elicitation study will be conducted to develop a theory of planned behavior-based questionnaire. This will be used in a survey to determine the factors influencing healthcare workers' intention to check the blood pressure of adolescents living with HIV. A cluster-randomized study will be conducted to assess the effect of a theory of planned behavior-based intervention on healthcare worker adherence to the guidelines as well as the blood pressure and arterial stiffness of adolescents living with HIV after a six-month follow-up period.

# **CHAPTER 1: INTRODUCTION**

## **1.1 Hypertension in adults and adolescents**

Hypertension is the leading modifiable risk factor for cardiovascular disease (CVD)-related disability and mortality globally. Each 10 mmHg increase in systolic blood pressure (BP) is associated with a 45% higher risk of ischemic heart disease and about a 65% higher risk of ischaemic or haemorrhagic stroke in those aged 55–64 years(Singh et al., 2013). In 2019, it was estimated to have accounted for 10.8 million deaths (19.2% of total deaths) and 235 million disability-adjusted life years (9.3% of total disability-adjusted life years) worldwide(Abbafati et al., 2020; Mills et al., 2020).

Although thought to be an adult disease, arterial hypertension is established early in life, with a rising prevalence alongside the obesity pandemic. Its prevalence has been reported to range from 0·2–24·8% among adolescents in Sub Saharan Africa(Noubiap et al., 2017) and 9.1% among adolescents in the Ashanti Region of Ghana(Noubiap et al., 2017; Sekyere & Abena, 2018). Elevated BPs in childhood and adolescence predict adult hypertension and increase the risk for cardiovascular morbidity and mortality in adulthood(Oh & Hong, 2019). Children and adolescents with a single BP measurement >90th percentile for the age, sex, and height are 2.4 times more likely to have an adult BP >90th percentile. Early detection, prevention and treatment of adolescent elevated BP could eliminate 10% of adult elevated BPs (Bao et al., 1995a; Kelly et al., 2015; Lauer et al., 1993). In addition to poor dietary and physical activity behaviours, one emerging risk factor for developing hypertension is HIV infection (Benzekri et al., 2018; Kwarisiima et al., 2016).

## **1.2 HIV, Cardiovascular diseases (CVD) and hypertension**

Although AIDS-related deaths have markedly reduced with increased access to antiretroviral care, their CVD-related morbidities are rising(Alonso et al., 2019). Compared to uninfected persons, they experience a higher incidence(per 1000 person-years) of CVD-related admissions( 10.8 vs 5.9), myocardial infarction( 1.4 vs 1.1), heart failure( 3.5 vs 1.1), stroke( 1.4 vs 0.5) and atrial fibrillation( 3.5 vs 2.9) (Alonso et al., 2019). Contributing to this is the higher prevalence of hypertension amongst persons living with HIV(PLHIV)(Bigna et al., 2020; K. Davis et al., 2021; Gebrie, 2020).

A recent meta-analysis of data from around the globe demonstrated that 35% of all HIV-infected adults on ART have hypertension, compared with an estimated 30% of HIV-uninfected adults(Xu et al., 2017). More than half of antiretroviral(ARV)-experienced individuals over 50 years are estimated to have hypertension(Fahme et al., 2018; Mbuthia et al., 2021; Pierre et al., 2019). In addition to the traditional modifiable and non-modifiable risk factors for hypertension, ARV- and HIV-associated microbial translocation, chronic inflammation, immune reconstitution, dyslipidemia, renal disease, and neuroendocrine response lead to endothelial dysfunction, accelerated vascular ageing and arterial stiffness(Fahme et al., 2018).

With a reported incidence(per 1000) of 10- 16 per month after ART initiation, the duration of HIV infection is a significant determinant in the development of hypertension, causing perinatally- and behaviorally- infected adolescents to have higher odds of being hypertensive(Mulugeta et al., 2021; Rodríguez-Arbolí et al., 2017). Adolescents living with HIV(ADLHIV) have been shown to have a higher prevalence of hypertension compared to their uninfected age and sex-matched peers(Chatterton-Kirchmeier et al., 2015; Oh & Hong, 2019). Therefore, the Expert Panel on Integrated Guidelines for Cardiovascular Health and Risk Reduction in Children and Adolescents classified HIV infected children and adolescents as being at moderate risk of CVD, especially hypertension, and called for increased surveillance (De Jesus, 2011b).

Several clinical practice guidelines have been developed for service providers to guide hypertension surveillance among children and adolescents. The most referenced is the Fourth Report by the National High Blood Pressure Education Program (NHBPEP) Working Group on Children and Adolescents(Falkner & Daniels, 2004), which informed the recommendations in Ghana’s Standard Treatment Guidelines(GHS, 2017).

## **1.3 Guidelines for screening and management of hypertension among children and adolescents.**

The guideline defines hypertension in children and adolescents as systolic BP (SBP) or diastolic BP (DBP), which is, on repeated measurement, at or above the 95th percentile for age, sex and height. BP between the 90th and 95th percentile in childhood and adolescence is designated “prehypertensive”. It also provides reference ranges to guide the classification of BP in children and a detailed follow-up plan based on the classification given. In addition, it captures recommendations on the frequency of screening, diagnosis, investigation and management of hypertension among them(Falkner & Daniels, 2004).

## **1.4 Adherence to clinical practice guidelines**

Despite the availability of these guidelines and their adaptations by countries and professional societies, adherence to it by healthcare workers has been generally poor(De Jesus, 2011a; Hagan et al., 2007; Lurbe et al., 2019). There are reports of unchecked blood pressures during two-thirds of adolescent clinic visits(Shapiro et al., 2012), over 80% of hypertensive adolescents not being recognized by healthcare workers (Brady et al., 2010) and about 75% of hypertensive adolescents not being appropriately classified and diagnosed(Hansen et al., 2007). Patient-, provider- and clinic-related factors have been identified as contributing to non-adherence to the clinical practice guidelines(Brady et al., 2010).

Educational, community-based, practice-based and multi-component strategies have been employed to help improve healthcare worker adherence, with differential outcomes(Davis & Taylor-Vaisey, 1997). However, a systematic review by Davis and Taylor recommends interventions targeting predictors of provider behaviour towards these guidelines(Davis & Taylor-Vaisey, 1997). One model which has guided the exploration of healthcare worker intentions to adhere to various guidelines is the Theory of Planned Behavior(TPB)(Ajzen, 1991).

## **1.5 Theory of planned behaviour**

The theory postulates that the likelihood of individuals engaging in a behaviour (e.g. checking the BPs of adolescents) correlates with the strength of their intention to engage in the behaviour. A behavioural intention represents the person’s commitment to act and is itself the outcome of

- the person’s attitudes toward the behaviour (attitude towards adolescent BP screening),
- the person’s perception of subjective group norms concerning the behaviour (subjective norms influencing adolescent BP screening), and
- the extent to which the person perceives him- or herself to have control concerning the behaviour (perceived behavioural control to check BPs of adolescents).

It also states that perceived behavioural control can directly influence behaviour without affecting intentions to perform the behaviour (Fishbein, 2012).

## **1.6 Problem statement**

Ghana is currently in epidemiological transition and is progressing rapidly with urbanization (Agyei-Mensah & Aikins, 2010); stroke and ischemic heart disease rose from being the seventh and ninth leading causes of death respectively in 2000 to take the third and fourth positions in 2019(WHO, 2020b). Contributing to this is the double burden of infectious and non-communicable diseases that increase CVD risk, especially hypertension(Agyei-Mensah & Aikins, 2010; Bosu & Bosu, 2021a).

Hypertension is among the leading causes of morbidity and mortality in Ghana(GHS, 2018; Nuamah et al., 2017), and the outpatient burden has been increasing. In the Greater Accra Region, new cases increased 3.8-fold in five years, from 35,855 in 2006 to 138,040 in 2010(Opare et al., 2013). It was the third leading cause of admissions and the leading cause of death, accounting for 4.7% of the total admissions and 15.3% of the total deaths in Ghana in 2017(GHS, 2018). It is the main determinant of stroke in the country, with a population attributable risk of about 91%(Owolabi et al., 2018). However, approximately two-thirds of hypertensives in the country are undiagnosed(Bosu & Bosu, 2021b).

Adding to the hypertension burden in the country is the increasing HIV burden. With a pooled prevalence of 30.3% (95% CI 26.1–34.8%) among the general population(Atibila et al., 2021) and  41.3% [95% CI, 35.2-47.3] among adult clients on antiretroviral therapy(ART) (Nartey, 2021), HIV is a significant contributor to the hypertension caseload in the country and thus needs to be given much attention.

Although Ghana’s sixth standard treatment guidelines provide directions on diagnosing and managing hypertension among children and adolescents(Andy, 2010), healthcare workers' level adherence to this guideline is unknown. This information is crucial because, in addition to the increase in the prevalence of known traditional risk factors, adolescents in Ghana generally have a relatively higher risk of hypertension due to in utero exposure to malaria(Ayoola et al., 2014; Bedu-Addo et al., 2017; Etyang et al., 2019). .

Concerning adolescents living with HIV, over 80% of the 23,000 in the country had the infection perinatally(UNAIDS, 2021a) and thus have more prolonged exposure to the virus and metabolic effects of the antiretrovirals. This makes them more likely to develop hypertension, especially those exposed to lopinavir- and dolutegravir-based regimen(WHO, 2021a).

The call by WHO to integrate hypertension and diabetes management into HIV services and the support for task shifting in HIV and hypertension care in the country (BeLue et al., 2009; P. Patel et al., 2018; UNAIDS, 2008; WHO, 2020a) provide a healthy policy environment for reducing the future burden of hypertension among these adolescents and for protecting those already hypertensive from the negative impact of COVID-19 through early diagnosis and appropriate management.

## **1.7 Justification**

The Greater Accra Region has over a quarter(28%) of the adolescents living with HIV in the country(Ghana AIDS Commission, 2021b). The ART-providing facilities in the Region will therefore be an excellent place to undertake an assessment of the level of healthcare worker adherence to the guidelines, and to identify contextual factors contributing to differential adherence among them, based on the theory of planned behaviour. Findings from the study will help develop an evidence-based intervention to improve healthcare workers' adherence to clinical practice guidelines and provide a framework to guide the effective dissemination of these guidelines in the country.

## **1.8 Research questions**

To help reduce the anticipated hypertension-related morbidities and mortalities among adolescents living with HIV, adherence to the guidelines for screening and management of hypertension among children and adolescents is critical at facilities providing ART services. This study, therefore, seeks to answer the following questions concerning ART sites in the Greater Accra Region:

1. Do service providers at ART sites adhere to the guidelines for screening and management of hypertension among adolescents?
2. What factors influence adherence to guidelines for screening and management of hypertension among adolescents?
3. Will a theory of planned behaviour-based intervention for service providers at ART sites improve adherence to guidelines for screening and management of hypertension among ADLHIV?
4. Will a theory of planned behavior-based intervention for service providers at ART sites improve the arterial stiffness of adolescents living with HIV who are found hypertensive?

## **1.9 Aim and objectives**

The overall aim is to improve the adherence to the CPG for diagnosis & management of hypertension among ADLHIV at selected ART sites in the Greater Accra Region.

The objectives are to

- 1. Determine the factors influencing adherence to the CPG for screening & management of hypertension among ADLHIV
  2. Assess the effect of a Theory of Planned Behavior-based intervention on HCW adherence to guidelines for screening & management of hypertension among ADLHIV
  3. Assess the effect of a Theory of Planned Behavior-based intervention on the arterial stiffness of ADLHIV found to have high BP.

## **1.10 Study hypothesis**

The hypotheses that will be tested in the study are as follows:

1. There is no difference in the proportion of adolescent ART visits that had BPs checked between facilities exposed to the intervention and unexposed facilities.
2. There is no change in arterial stiffness parameters of hypertensive adolescents living with HIV after six months of exposure to the TPB- based intervention.

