### **3.3.1 Study Design**

This will be a multi-facility, two-arm cluster-randomized study and will follow the CONSORT guidelines for the conduct of cluster randomized studies(CONSORT, 2010). There will be random allocation by clusters (health facilities) to the control and intervention arms of the study.

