#### **b.Secondary outcomes**

The secondary outcomes of the study will assess the effect of the intervention on the adolescents living with HIV at the intervention facility. A cross-sectional survey and physiological assessments will be conducted among 20 randomly selected adolescents per facility at baseline and six months after the intervention in both arms of the study.

1. **Cross-sectional Survey among Adolescents Living with HIV**

This survey will validate the data extracted from the records and confirm that the adolescents received the interventions. Data will be collected by face-to-face interviews using a structured questionnaire based on an adaption of the WHO STEPS Questionnaire for Chronic Disease Risk Factor Surveillance(WHO, 2012). The questionnaire will collect data on; socio-demographic characteristics, history of tobacco use and alcohol consumption, physical activity, diet and anthropometric measurements. In addition, data will be collected to assess the

- Number of clients who reported having their BPs checked during the last clinical visit
- Number of clients who reported being educated on hypertension and its risk reduction during the last clinical visit and
- The number of clients who reported adhering to any preventive measures (diet, physical activity) in the week prior to the interview.

Height and weight measurements of respondents will be taken with calibrated stadiometers and a weighing scale, respectively. All measurements will be taken using the US Centers for Disease Control and Prevention (CDC) standard procedure(CDC, 2014).

1. **Physiological Assessments**

These assessments will identify adolescents with normal blood pressure, masked hypertension, white coat hypertension, elevated BP and high BP as defined in the guideline for screening and managing hypertension among children and adolescents(Flynn et al., 2017). The assessment will also help identify those at risk of being hypertensive (having arterial stiffness). These will be achieved by measuring their office blood pressure, ambulatory blood pressure and cardio-ankle vascular index (arterial stiffness) as described below.

- **Office Blood pressure**

Participants’ blood pressure will be assessed as recommended in the guideline for screening and managing hypertension among children and adolescents(Flynn et al., 2017) and described in section **2.6.3.**

- **Ambulatory blood pressure measurement(ABPM)**

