This will be performed using the CONTEC ABPM50 24H Ambulatory Blood Pressure Monitor. It will be done over 24 h, with BP readings every 30 min. A minimum of 70% accurate readings will be considered sufficient. Wake and sleep periods will be based on sleep and wake times recorded in the participant’s journal. Height-specific ABPM percentiles presented in the guidelines(Flynn et al., 2017) and associated references will be used to define ABPM abnormal BP threshold values and percentiles and to define ABPM-specific BP abnormalities(Fredric et al., 2021).

- **Cardio-Ankle Vascular Index**

This will be assessed using the VaSera 1500N vascular screening system (Fukuda Denshi Co.). As recommended, examinations will be conducted under standard conditions (room temperature 22 °C, minimization of stimuli) between 8.00 and 10.00 a.m. Participants will be instructed to avoid physical exercise and consumption of substances that could affect cardiovascular function (e.g., caffeine, alcohol) 24 hours prior to the examination. Before the examination, participants will rest in a supine position for 15 minutes to avoid the potential effects of stress. At the time of examination, subjects will remain supine with both arms on the bed, parallel to the body, and limb cushions placed below the elbows and heels to prevent contact of the limb cuffs with the bed. Electrocardiographic electrodes will be placed on both wrists, oscillometric blood pressure (BP) cuffs wrapped around the arms and ankles, and a microphone for phonocardiography placed on the sternum at the level of the second intercostal space. The cardio-ankle vascular index will be measured to determine the presence of arterial stiffness based on age- and sex-defined cut-offs(Rico Martín et al., 2020).

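### Hypothesis 2 is worded as a before-after change in exposed hypertensive adolescents with no comparator, although the objective is the effect of the intervention and both arms are measured

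*Protocol*

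**What the plan says.** Section 1.10 lists two hypotheses for testing. The first is a contrast of arms: it compares screening "between facilities exposed to the intervention and unexposed facilities". The second is not: "There is no change in arterial stiffness parameters of hypertensive adolescents living with HIV after six months of exposure to the TPB- based intervention". It speaks only of exposed adolescents and only of change over time.

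The rest of the protocol points to a comparison of arms:

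- Section 3.3.1: "This will be a multi-facility, two-arm cluster-randomized study".
- Section 3.3.9 b: "physiological assessments will be conducted among 20 randomly selected adolescents per facility at baseline and six months after the intervention in both arms".
- Section 1.9, objective 3: "Assess the effect of a Theory of Planned Behavior-based intervention on the arterial stiffness of ADLHIV found to have high BP". Research question 4 in section 1.8 asks the same of adolescents found hypertensive.
- Section 3.3.8: facilities in both arms receive the guideline orientation. Only the intervention arm receives the theory-based package on top (section 3.3.7).

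The Study Summary gives objective 3 a different scope: "Assess the effect of a Theory of Planned Behavior-based intervention on the arterial stiffness and blood pressure of ADLHIV". That covers all adolescents living with HIV and adds blood pressure as an outcome.

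Section 3.4.2 lists independent-sample t-tests, ANOVA, a z-test and logistic regression in general terms. It ties none of them to CAVI, to arm or to change from baseline.

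**The concern.** Objective 3 asks what the intervention does. A null of no change within the exposed group can be false for reasons unrelated to the intervention package:

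1. Any drift over six months that both arms share, such as growth, antiretroviral regimen changes or measurement drift.
2. Any effect of the guideline orientation, which both arms receive. Change within the intervention arm mixes it with the package, and only the contrast of arms separates them.
3. Regression to the mean, because the group is picked for a high measured blood pressure and CAVI may be correlated with it. This applies if the same adolescents are measured twice.

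The error also runs the other way. If stiffness worsens in control facilities and holds steady in intervention facilities, that is a benefit, but hypothesis 2 would record it as no change.

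This is one of only two stated hypotheses and the only one about a patient outcome. As worded, rejecting it would not support a claim that the intervention works.

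**Working it through.** **The plan's own figure.** The protocol gives no sample size for hypothesis 2. Its calculation in section 3.3.5 serves hypothesis 1, and it reproduces. For 17% versus 34%, two-sided 5%, 80% power and pooled variance, n = 103 per arm. The design effect is 1 + (20 - 1) x 0.05 = 1.95. Then 103 x 1.95 = 200.9 per arm, or 10.04 facilities of 20, against 10 stated. It has no bearing on the wording of hypothesis 2.

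**Number of hypertensive adolescents in the intervention arm.** 12 facilities x 20 = 240. The protocol cites a hypertension prevalence of 10.5% in adolescents living with HIV (section 2.5.4) and a global pooled 4.0% at ages 10-17 (section 2.4.1). Applying either to this sample is an assumption: 240 x 0.105 = 25.2 and 240 x 0.04 = 9.6, so about 10 to 25.

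**Shared drift, no intervention effect.** Let d be the mean change common to both arms, in SDs of change (assumed 0.2 to 0.5). A one-sample t-test of change at two-sided 0.05 has noncentrality d x sqrt(n). For n = 25 this is 1.0, 1.5 and 2.5. Rejection of the no-change null:

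| n | d = 0.2 | d = 0.3 | d = 0.5 |
|---|---|---|---|
| 25 | 16% | 30% | 67% |
| 10 | 9% | 14% | 29% |

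**Regression to the mean alone, no drift and no intervention effect.** Assume selection of the top 10.5% on baseline blood pressure (mean z = 1.73). Let r be the correlation of blood pressure with CAVI at baseline. The correlation of baseline blood pressure with six-month CAVI is taken as 0.7r. Let rho be the CAVI test-retest correlation. Expected CAVI change = r x (0.7 - 1) x 1.73, which is -0.16 SD for r = 0.3 and -0.26 SD for r = 0.5. Simulated rejection at n = 25 (4,000 replicates, clustering ignored):

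| r | rho | Before-after test | Between-arm test of change |
|---|---|---|---|
| 0.3 | 0.6 | 14% | 4.8% |
| 0.3 | 0.8 | 23% | 4.9% |
| 0.5 | 0.6 | 31% | 5.0% |
| 0.5 | 0.8 | 52% | 4.5% |

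**The reverse case.** If controls worsen by any amount and the intervention arm stays flat, the before-after test rejects at its nominal 5%, whatever the size of the benefit.

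**Precision of a between-arm comparison.** Detectable difference at 80% power = 2.8 x sqrt((2 x DE / n) x (1 - c^2)), with baseline-to-follow-up CAVI correlation c = 0.6 (assumed) and the protocol's ICC of 0.05 carried over to CAVI (assumed).

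- Hypertensive adolescents only, n = 25 per arm, about 2 per facility, DE = 1.05: 2.8 x sqrt((2 x 1.05 / 25) x 0.64) = 0.65 SD.
- All sampled adolescents, n = 240 per arm, DE = 1.95: 2.8 x sqrt((2 x 1.95 / 240) x 0.64) = 0.29 SD.
- An effect of 0.65 SD confined to 10.5% of adolescents averages 0.65 x 0.105 = 0.07 SD over everyone.

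**The case against.** The strongest reply is that the sentence is only loosely worded. Section 3.4.2 lists no paired test, its t-tests are for independent samples, and section 3.3.9 b presents the secondary outcomes as the effect of the intervention, measured "at baseline and six months after the intervention in both arms of the study". So a reader might infer that the sponsor has decided to discard the control arm, and the documents do not support that. What stands is narrower. The protocol states a null for testing, that null has no comparator, and no other section restates it as a contrast of arms.

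Other stronger readings also go too far:

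- *Regression to the mean is certain and large.* It depends on assumed correlations and on measuring the same adolescents twice. Sections 3.3.4 and 3.3.6 suggest one sample for both surveys, while section 3.3.9 b calls the survey cross-sectional. Repeated readings, confirmation over three visits (section 2.6.3) and ambulatory monitoring would shrink it. They would not remove a time trend or the shared orientation.
- *The size can be read from blood pressure itself.* The fall would be larger there, since it is the selection variable, but hypothesis 2 concerns arterial stiffness.
- *CAVI will be analysed only as a binary variable.* Section 3.3.9 b uses it "to determine the presence of arterial stiffness based on age- and sex-defined cut-offs". That is a classification and does not rule out analysing the continuous value.
- *The random 20 per facility is a conflicting population.* It is the sample in which hypertensive adolescents are identified.
- *The main question should move to all adolescents.* Sections 1.8 to 1.10 target those with high blood pressure. The smaller detectable difference in the full sample (0.29 versus 0.65 SD) is for a different quantity. An effect confined to hypertensive adolescents would dilute to about 0.07 SD and be missed.

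**Conclusion.** The point holds as a defect in the stated hypothesis. It is not a defect in data collection, and there is no evidence of a planned paired analysis. Hypothesis 2 as worded cannot answer objective 3 or research question 4. With about 25 hypertensive adolescents and no intervention effect, the before-after test on CAVI would reject in roughly 14-67% of trials instead of 5%. With about 10 adolescents, the drift figures fall to 9-29%. These ranges rest on assumed drifts of 0.2-0.5 SD of change, the assumed correlations above, a prevalence borrowed from elsewhere in the protocol, and no clustering. The regression-to-the-mean part (14-52%) also needs the same adolescents at both times. The direction of the problem does not depend on these values, but its size does.

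The mismatch between the Study Summary (all adolescents, stiffness and blood pressure) and sections 1.8 to 1.10 (high-blood-pressure or hypertensive adolescents, stiffness only) is real and should be settled at the same time.

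This should be fixed. It falls short of a must-fix because the outcome is secondary, hypothesis 1 is correctly between arms, and control data are already planned.

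**What to change.** 1. Restate hypothesis 2 in section 1.10 as no difference between arms in six-month CAVI among adolescents with high blood pressure at the research team's baseline assessment, adjusted for each adolescent's own baseline CAVI and allowing for clustering by facility. Defining the group from the team's baseline measurement matters because the intervention is meant to raise detection by facility staff. A group defined by later facility diagnosis could differ between arms.
2. Add a matching line to section 3.4.2.
3. Make the Study Summary and sections 1.8 to 1.10 name the same population and the same outcomes.
4. State whether the same adolescents are measured at both times, reconciling sections 3.3.4 and 3.3.6 with the cross-sectional label in section 3.3.9 b. The baseline adjustment depends on this.
5. Optionally add a between-arm comparison in all sampled adolescents as a secondary analysis.

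The cost is wording only, since no new measurements or participants are needed. The price in precision should be acknowledged: about 25 hypertensive adolescents per arm can detect only about 0.65 SD under the assumptions shown, so a null result would not be informative about smaller effects.

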### **3.3.8 Comparator**

All 24 facilities will be given an orientation on the guidelines for screening and managing hypertension among children and adolescents. This will be done by trained facilitators using PowerPoint presentations, group discussions and case scenarios.

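### Hypothesis 2 is worded as a before-after test in exposed adolescents with no comparator, although the trial is randomised and measures arterial stiffness in both arms

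*Protocol*

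**What the plan says.** Section 1.10 introduces two null hypotheses as those the study will test. The first concerns BP checks at visits and is a comparison "between facilities exposed to the intervention and unexposed facilities". The second reads: "There is no change in arterial stiffness parameters of hypertensive adolescents living with HIV after six months of exposure" to the intervention. It is the only hypothesis that serves objective 3, which section 1.9 words as: "Assess the effect of a Theory of Planned Behavior-based intervention on the arterial stiffness of ADLHIV found to have high BP". Research question 4 in section 1.8 likewise asks whether the intervention improves stiffness in adolescents found hypertensive.

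The design is comparative. Section 3.3.1 says: "This will be a multi-facility, two-arm cluster-randomized study". Section 3.3.9b opens by saying the secondary outcomes will "assess the effect of the intervention on the adolescents living with HIV at the intervention facility", but its next sentence schedules the survey and physiological assessments, including the cardio-ankle vascular index, at baseline and "six months after the intervention in both arms of the study". Section 3.3.8 adds a component that both arms share: "All 24 facilities will be given an orientation on the guidelines".

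Section 3.4.2 lists general tests. For means it gives independent-sample t-tests or one-way ANOVA. It does not say which contrast belongs to hypothesis 2.

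**The concern.** Adolescents at control facilities are not exposed to the package, so a null of no change after exposure concerns the intervention arm alone. A six-month change in that arm mixes the package effect with whatever would have happened anyway. Three such sources are built into this design:

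- the participants are growing adolescents;
- the group is defined by high BP, so BP is expected to move back towards the mean, and stiffness with it to the extent that the two are correlated;
- every facility receives the guideline orientation.

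Rejecting the hypothesis would therefore not answer objective 3 or research question 4. Failing to reject would not answer them either, because a package that only slows a worsening could show as no change. What is at stake is the protocol's only stated hypothesis on patient benefit. It could yield a claim that the randomisation does not support, while control data that would settle the matter are already being collected.

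**Working it through.** **Plan's own figure.** The protocol gives no effect size, SD or sample size for hypothesis 2. Its only calculation (section 3.3.5) is for BP screening: 17% against 34%, two-sided 5%, 80% power, 20 adolescents per facility, ICC 0.05. The pooled two-proportion formula gives 102.0 per arm. The design effect is 1 + 19 × 0.05 = 1.95, so 102.0 × 1.95 / 20 = 9.95 facilities per arm. This matches the stated 10, and nothing in this point disturbs it.

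**Size of the hypothesis 2 group.** There are 12 facilities × 20 = 240 adolescents per arm. Among the prevalences the protocol quotes are 4.0% (section 2.4.1, pooled global figure for ages 10 to 17) and 10.5% (section 2.5.4, adolescents living with HIV in Lagos). 240 × 0.040 = 9.6 and 240 × 0.105 = 25.2, so about 10 to 25 hypertensive adolescents per arm, or roughly 1 to 2 per facility.

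**Before-after test with no package effect.** Suppose a shared shift of d SD of the change score. The paired t statistic then follows a noncentral t with n − 1 degrees of freedom and noncentrality d√n. The value of d is assumed, because the protocol gives nothing from which to derive it.

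| d (assumed) | n = 10 | n = 25 |
|---|---|---|
| 0 | 5% | 5% |
| 0.2 | 8.8% | 16.1% |
| 0.3 | 13.6% | 30.2% |
| 0.5 | 29.3% | 67.0% |

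For example, at d = 0.3 and n = 25 the noncentrality is 0.3 × 5 = 1.5, the critical value is 2.064 and the two-sided rejection rate is 30.2%. The rejections fall almost entirely in the direction of the shift, which the protocol does not allow us to predict.

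**Regression to the mean, for BP.** If a fraction p lies above the cut-off, the mean of a standard normal above it is φ(c)/p, and the expected untreated fall is (1 − r) × φ(c)/p for a correlation r between the two occasions. With r assumed at 0.8 to 0.6:

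- p = 5%: mean 2.06 SD, fall 0.41 to 0.83 SD;
- p = 10.5%: mean 1.73 SD, fall 0.35 to 0.69 SD.

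These are SDs of BP, not of arterial stiffness.

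**Carry-over to stiffness, and the between-arm test.** Simulation used 240 per arm, the top 10.5% on baseline BP selected, no package effect and no clustering. It assumed a BP correlation over time of 0.5 or 0.7, a stiffness-BP correlation of 0.2 to 0.6 and a stiffness correlation over time of 0.7. The before-after test rejected in 10% to 91% of runs. The between-arm test of change on the same data rejected in 4.5% to 5.7%. The width of the first range shows how far it depends on the assumptions. The second stays near 5% throughout, because a shared change cancels between arms.

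**Power of the between-arm comparison.** A two-sample t-test at two-sided 5% and 0.5 SD has noncentrality 0.5√(n/2). With n = 10 per arm this is 1.118 and power is 19%. With n = 25 it is 1.768 and power is 41%. Clustering is ignored in both.

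**The case against.** The strongest reply is that only one sentence is at fault. The Study Summary says a cluster-randomised study will assess the effect on blood pressure and arterial stiffness, and the control arm's physiological measurements have no evident purpose except comparison. Section 3.4.2 lists only independent-group tests for means and no paired test, so a between-arm analysis may well be what is intended. The exact contrast for a secondary outcome is often left to an SAP, and the study flow chart is not visible. All of this stands. A reader might infer that the trial has no control comparison for arterial stiffness, or that a paired test is planned. The documents support neither.

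The numbers also have limits. The shift sizes are assumed. The regression-to-the-mean figures are for BP, and no figure in the protocol links them to stiffness. The guideline procedure in section 2.6.3 repeats elevated readings and averages the last two, and 24-hour monitoring is used as well; both would reduce regression to the mean. A paired test needs the same adolescents at both rounds. Section 3.3.6 suggests one sample for both, while section 3.3.9b can be read as two cross-sectional samples. Extending the test to all 240 adolescents would fall outside hypothesis 2, which covers hypertensive adolescents only.

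What does not stand is that the rest of the protocol cures the wording. Section 1.10 says these are the hypotheses to be tested, the comparator is present in hypothesis 1 and absent from hypothesis 2, and nothing in section 3.4.2 ties a between-arm contrast to the latter. An SAP that implemented hypothesis 2 as written would carry the fault forward.

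**Conclusion.** The point holds as a fault in one stated hypothesis, not in the design or the data collection. As worded, hypothesis 2 cannot answer objective 3, because any change shared by both arms could be read as an intervention effect. The direction of this conclusion needs no assumed figure, but its size does. The 14% to 30% rejection rate rests on a shared shift of 0.3 SD, a paired test, and 10 to 25 hypertensive adolescents in the intervention arm. The actual size cannot be known from the protocol.

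A reader might infer that the trial would falsely report better arterial stiffness. That goes too far: the shared shift could be a worsening, and the analysis may turn out to be between arms. Arterial stiffness is a secondary outcome, and the primary outcome, hypothesis 1 and the sample size are untouched. The correction is worth making before analysis because it is cheap and the sentence is wrong as it stands.

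**What to change.** Restate hypothesis 2 as: *Among adolescents living with HIV found to have high BP at baseline, there is no difference between intervention and control facilities in arterial stiffness (cardio-ankle vascular index) at six months, adjusted for its baseline value.* Analyse it with facility as the randomised unit. Keep the high-BP restriction: section 1.9 and research question 4 define the population that way, and a version covering all adolescents would no longer match them. The baseline adjustment also requires the same adolescents to be measured at both rounds, so section 3.3.9b should say so.

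Reword the first sentence of section 3.3.9b as a comparison of adolescents at intervention and control facilities. Report within-arm change descriptively only, with no test and no claim of effect.

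The cost is a few sentences in the protocol, with no added participants or measurements. The drawback should be stated openly. With about 10 to 25 adolescents with high BP per arm, power is only about 19% to 41% at 0.5 SD before clustering. The result should be presented as a secondary estimate with its confidence interval, and a non-significant result should not be read as evidence of no effect.
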